#### Outcomes

Outcomes to be measured are as follows:COPD exacerbation: to be defined using a CPRD-HES algorithm developed previously by authors of this study protocol.^10^
All-cause mortality: as recorded in Office of National Statistics (ONS) mortality statistics (data that is linked to CPRD data).Pneumonia: as defined using a CPRD-HES algorithm published previously by authors of this study protocol.^11^
Time to COPD treatment change: determined by prescribing records indicating the start of a new, additional COPD treatment.

#### Covariates

Covariates to be considered for inclusion in the propensity score include the following (all obtained from CPRD data):Lung function (FEV_1_, FEV_1_/FVC)AgeGenderBody mass indexAlcohol consumptionVascular disease (broken into individual components, eg, hypertension, heart failure, atherosclerotic disease)Use of prescribed aspirin and statinsPrior treatment with other COPD medicationType 2 diabetesHistory of cancerRenal diseaseHealthcare utilisation intensity (number of prior visits, hospitalisations, number of distinct medications used, number of procedures).

### Sample size

#### Objective 1

Assuming a baseline conservative exacerbation rate of 0.5 per patient per year,^10^ we would only require a sample of 408 patients per treatment group to detect a reduction in annual exacerbation rate to 0.4 per year, with 80% power and 5% significance. The estimated sample size is ~12 000, which will provide ample power for the main outcomes of interest, and allow stratification by patient characteristics to determine stratified results, and will also be ample for the secondary analyses where we will use 99% CIs. For example, to detect a reduction from 0.5 to 0.4 exacerbations per year with 80% power and 1% significance we would need ~600 people in each treatment group.

#### Objectives 2 and 3

We are also confident that we will have sufficient numbers to allow well-powered analyses for objectives 2 and 3. For example, a feasibility count looking at the number of people over the age of 80 eligible for inclusion in objective 2 estimated that there would be >2000 people in each exposure group.

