Each untreated patient derived in step 3 (n~6000) will be matched 1:1 with the FP/SAL-treated patient record from step 4 with the closest propensity score (~12 000) giving us an analysis population for objective 1 of ~12 000 patients—double the size of TORCH (figure 2). For those individuals that have contributed multiple exposed records to the pool of CPRD-exposed participants (figure 3), after one of their exposed records has been propensity-score matched to an unexposed participant, we will remove all other exposed records for that individual from the remaining pool of CPRD-exposed participants. This will mean that an individual can only appear once as an exposed participant in the final propensity-score matched cohort.

We will also apply an alternative additional approach for objective 1, where instead of generating and using propensity scores to obtain a final analysis population at steps 5 and 6, we will match records from our exposed TORCH-eligible cohort with participants from the TORCH trial to create a TORCH-analogous exposed patient cohort. This will then be combined with the TORCH-analogous unexposed patient cohort to create a final analysis population (with multivariable regression techniques used to account for confounding instead of propensity scores).

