#### Methods of analysis

For all objectives, comparisons will be made according to FP/SAL (or other drugs being analysed as specified in the ’Exposures' section) status for rate of COPD exacerbation, pneumonia and mortality over 3 years. All analyses will be performed according to the ‘intention-to-treat’ principle (as was done in the TORCH study), meaning that if a participant enters the study as either an exposed or unexposed participant, they will remain assigned to that exposure category for the entire duration of their follow-up (irrespective as to whether their true exposure status changes). For exacerbations, a negative binomial model will be used, accounting for variability between patients in the number and frequency of exacerbations, with the number of exacerbations as the outcome and the log of treated time as an offset variable. Time to mortality, first pneumonia and treatment change will be analysed using Cox proportional hazards regression. This mirrors TORCH end points of major benefit and harm. We anticipate the propensity matching process will allow us to assemble treated and untreated groups that are very similar with respect to baseline characteristics except FP/SAL treatment status. However, this will be tested by assessing standardised differences for each baseline variable. If substantial differences are noted for important variables, it may be necessary to further adjust the statistical models. This could also include examining the effect of using greedy versus optimum matching approaches in order to obtain the closest propensity score match and/or matching at a ratio other than 1:1.^17^

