#### Validation of results against TORCH

We will validate our findings against TORCH as part of objective 1 by determining whether results of the CPRD FP/SAL versus no FP/SAL treatment analysis are compatible with the TORCH exacerbations rate ratio for FP/SAL versus placebo (0.75; 95% CI 0.69 to 0.81). This outcome has been selected as it is an outcome of key significance for people with COPD^4^ and the result in TORCH shows a clear benefit with 95% confidence limits below 1. We have set two criteria that must be met for us to conclude results are consistent. First, the effect size must be clinically comparable with TORCH findings; the rate ratio for exacerbations in CPRD must be between 0.65 and 0.9. This range is deliberately not symmetrical around the TORCH estimate of 0.75 as we would anticipate the treatment effect in routine clinical care may be weaker than that seen in the optimised setting of a randomised trial. We recognise this rule could be met with a poorly powered, inconclusive result, so a second criterion is that the 95% CI for the rate ratio must exclude 1. If we go on to compare FP/SAL with SAL alone (see the ’Exposures, outcomes and covariates' section, ’Exposures' subheading), the 95% CI would also need to exclude 1, and the rate ratio would need to be between 0.81 and 0.95 (compared with the TORCH FP/SAL vs SAL result of 0.88, 95% CI 0.81 to 0.95).

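### The 408 and ~600 per group match sizes for comparing two proportions (50% v 40%), not annual event rates of 0.5 v 0.4, so the stated 80% power is not supported for the planned negative binomial analysis

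*Protocol article*

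**What the plan says.** The article's Sample size section, under Objective 1, sets the comparator rate: "Assuming a baseline conservative exacerbation rate of 0.5 per patient per year". It then states that "we would only require a sample of 408 patients per treatment group to detect a reduction in annual exacerbation rate to 0.4 per year"; the power for this is given as 80% and the significance level as 5%. For the secondary analyses, which use 99% confidence intervals, it adds that for the same reduction "with 80% power and 1% significance we would need ~600 people in each treatment group". It names no formula, follow-up time or overdispersion. Against these figures it sets an expected total of about 12 000 patients and concludes that power is ample for the main outcomes, for stratified results and for the secondary analyses.

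Methods of analysis gives the model: "For exacerbations, a negative binomial model will be used, accounting for variability between patients in the number and frequency of exacerbations", with log time as an offset. The comparison is by exposure "status for rate of COPD exacerbation, pneumonia and mortality over 3 years".

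For objectives 2 and 3 the Sample size section cites a feasibility count of more than 2000 people aged over 80 in each exposure group.

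**The concern.** An annual rate of 0.5 exacerbations per patient is not a probability of 0.5. A yes/no outcome with probability 0.5 has variance 0.25. A count with mean 0.5 has variance of at least 0.5, and more if patients differ in their underlying rates, which is the reason the article gives for choosing a negative binomial model. A size from the proportions formula therefore answers a different question. It also leaves out the two quantities that govern power for a rate: time at risk and dispersion.

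These are the only required group sizes in the article. The main cohort is so large that the mistake does no harm there. The Exposures section, however, plans five further drug comparisons in objective 1 and six exposures in each of objectives 2 and 3. Objective 2 also plans separate cohorts (for example lung surgery, long-term oxygen, drug or alcohol abuse) for which no counts are given. In groups of that kind a reader could take 400 to 600 per arm as enough.

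**Working it through.** **Inputs from the article.** Rates 0.5 and 0.4 per patient-year (rate ratio 0.8); 80% power; 5% and 1% significance (Sample size). Equal groups: each untreated patient "will be matched 1:1 with the FP/SAL-treated patient record from step 4 with the closest propensity score" (Selection of participants, objective 1, Step 6). Sidedness is not stated; two-sided is inferred from the validation rule that "a second criterion is that the 95% CI for the rate ratio must exclude 1".

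**Assumptions, not in the article.** Mean follow-up T in years and negative binomial dispersion k (variance = mean + k × mean²).

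**Step 1: reproduce the stated figures.** Two proportions, pooled variance under the null, p̄ = 0.45, d = 0.1:

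n = [z_α/2 √(2 p̄(1−p̄)) + z_β √(p₁(1−p₁) + p₂(1−p₂))]² / d², then n_cc = (n/4)[1 + √(1 + 4/(n d))]².

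- 5%: n = (1.960 × √0.495 + 0.842 × √0.49)² / 0.01 = (1.3790 + 0.5891)² / 0.01 = 387.3. n_cc = (387.3/4)(1 + 1.0504)² = 407.1, so **408**.
- 1%: n = (1.8123 + 0.5891)² / 0.01 = 576.7. n_cc = (576.7/4)(1 + 1.0341)² = 596.5, so **597**, stated as ~600.

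**Step 2: do rate formulas also give 408?** At 5%, (z_α/2 + z_β)² = 7.849.

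- Poisson, rate difference, 1 year: 7.849 × (0.5 + 0.4) / 0.01 = 706.4, so 707.
- Poisson, log rate ratio, 1 year: 7.849 × (1/0.5 + 1/0.4) / (ln 0.8)² = 7.849 × 4.5 / 0.04979 = 709.3, so 710.
- A Poisson formula reaches 408 only at about 1.73 years of follow-up. A negative binomial formula at 3 years reaches it only with k of about 0.54. Neither value is in the article.

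**Step 3: size under the planned model.**

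n per group = (z_α/2 + z_β)² × [4.5/T + 2k] / (ln 0.8)², with (z_α/2 + z_β)² = 7.849 at 5% and 11.679 at 1%.

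| | k = 0 | k = 0.5 | k = 1 |
|---|---|---|---|
| 5%, T = 1 | 710 | 867 | 1,025 |
| 5%, T = 2 | 355 | 513 | 670 |
| 5%, T = 3 | 237 | 395 | 552 |
| 1%, T = 1 | 1,056 | 1,291 | 1,525 |
| 1%, T = 2 | 528 | 763 | 997 |
| 1%, T = 3 | 352 | 587 | 821 |

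**Step 4: power of the stated sizes.**

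Power = Φ( |ln 0.8| / √[(4.5/T + 2k)/n] − z_α/2 ).

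Example, n = 408, T = 3, k = 0.5: standard error √(2.5/408) = 0.0783; 0.2231/0.0783 = 2.851; Φ(2.851 − 1.960) = 0.81.

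| | k = 0 | k = 0.5 | k = 1 |
|---|---|---|---|
| 408 at 5%, T = 1 | 57% | 48% | 42% |
| 408 at 5%, T = 2 | 85% | 71% | 59% |
| 408 at 5%, T = 3 | 96% | 81% | 67% |
| 600 at 1%, T = 1 | 50% | 40% | 33% |
| 600 at 1%, T = 2 | 86% | 68% | 53% |
| 600 at 1%, T = 3 | 97% | 81% | 64% |

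**Step 5: dispersion at which 80% is just kept.** k* = [n (ln 0.8)² / (z_α/2 + z_β)² − 4.5/T] / 2.

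- 408 at 5%: T = 3, (2.588 − 1.5)/2 = 0.54; T = 2, (2.588 − 2.25)/2 = 0.17; T = 1, negative, so 80% is not reached at any dispersion.
- 600 at 1%: 0.53 at T = 3, 0.15 at T = 2, negative at T = 1.

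**Step 6: the sizes actually expected.** In the least favourable case tried (T = 1, k = 2), about 6000 per group gives above 99% power at both 5% and 1%. With 2000 per group, power is 93% at 5% and 80% at 1%.

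**The case against.** The strongest reply is that the planned comparison runs over 3 years. At T = 3 the count model needs only 237 (k = 0) or 395 (k = 0.5) per group at 5%, and 352 or 587 at 1%, all below the stated 408 and ~600. This stands. A reader might infer from the wrong formula that 80% power is lost under the planned analysis; the article does not support that. Power falls short at 1 year in every scenario, but at 3 years only if k exceeds about 0.54. Equally, 3 full years cannot be taken for granted. The article's description of the database ends follow-up at death, transfer out or the practice's last collection, and patients may be selected up to 1 January 2017. At a mean of 2 years the tolerable dispersion drops to about 0.17.

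A reader might also infer that objectives 2 and 3 rest on 408 or ~600. They do not: the article supports them with a feasibility count, and the one size it quotes is adequate in the scenarios tried. Nor does the article name any group of 400 to 600 that it judges sufficient, so the harm depends on how the figures are used.

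Finally, ~600 adds little as evidence for the formula. Scaling 408 by 11.679/7.849 gives 607, so most formulas would land near it. The diagnosis rests chiefly on the exact match at 408 and on the failure of rate formulas at 1 year to give that figure.

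**Conclusion.** The point holds as a correction to the stated figures, not as a finding that the study is underpowered. The article's 408 and ~600 agree with a continuity-corrected comparison of 50% with 40%, whereas the quantities described are annual event rates to be modelled as overdispersed counts over 3 years. The claim of 80% power therefore has no support in the article. Whether it is true depends on mean follow-up and dispersion, which are not given. Over T from 1 to 3 years and k from 0 to 1, true power at 408 per group (5%) lies anywhere from 42% to 96%, and at 600 per group (1%) from 33% to 97%.

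The ample-power conclusion survives for objective 1's main comparison, and the over-80 cohort is also adequate. The consequence is confined to smaller strata, secondary drug comparisons and small cohorts, if 408 or ~600 is taken as a sufficient size. The results assume a two-sided test, equal groups, a large-sample normal approximation for the log rate ratio and the same mean follow-up in both groups.

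**What to change.** Replace both figures with negative binomial sizes that state the expected mean follow-up and dispersion and show a range. For k from 0 to 1, per group: at 5%, 710 to 1,025 for T = 1 year and 237 to 552 for T = 3; at 1%, 1,056 to 1,525 and 352 to 821. Alternatively, drop the required sizes and report power or expected confidence interval width at the group sizes the feasibility counts suggest, which suits a cohort whose size is set by the available records.

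A minimum group size for running a stratum or drug comparison should not be added: the plan has no such rule, and the 1-year sizes do not match its 3-year horizon.

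The cost is less favourable stated figures in some scenarios. No more patients are needed, and the design, the model and the validation criteria do not change.

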### Statistical analysis

#### Propensity score for addressing confounding

The propensity score will be constructed using the principle that predictors of the exposure and outcome, or outcome only (mortality) should be included. We will consider a wide range of factors for inclusion (as listed in the ’Covariates' section), such as: age, sex, body mass index, alcohol consumption and a wide range of comorbidities (eg, type 2 diabetes, coronary heart disease, cerebrovascular disease, peripheral vascular disease, heart failure, hypertension, renal disease, cancer). We will further adjust for healthcare utilisation intensity (number of prior visits, hospitalisations, number of distinct medications used, number of procedures, etc) as these are generic correlates of disease state and the likelihood of recording completeness. We have substantial prior experience of building propensity models.^13–16^

For the additional alternative approach to objective 1 relying on matching of both unexposed and exposed patients to the TORCH trial patients (described in the ’Selection of participants—objective 1—step 6' section), we will use multivariable regression techniques to address confounding, considering a similar wide range of covariates for adjustment.

The variable list used for the propensity score model obtained in objective 1 will be the basis for propensity score modelling in objectives 2 and 3, but additional variables will also be considered given the different nature of the patient populations being studied in these objectives.

#### Methods of analysis

For all objectives, comparisons will be made according to FP/SAL (or other drugs being analysed as specified in the ’Exposures' section) status for rate of COPD exacerbation, pneumonia and mortality over 3 years. All analyses will be performed according to the ‘intention-to-treat’ principle (as was done in the TORCH study), meaning that if a participant enters the study as either an exposed or unexposed participant, they will remain assigned to that exposure category for the entire duration of their follow-up (irrespective as to whether their true exposure status changes). For exacerbations, a negative binomial model will be used, accounting for variability between patients in the number and frequency of exacerbations, with the number of exacerbations as the outcome and the log of treated time as an offset variable. Time to mortality, first pneumonia and treatment change will be analysed using Cox proportional hazards regression. This mirrors TORCH end points of major benefit and harm. We anticipate the propensity matching process will allow us to assemble treated and untreated groups that are very similar with respect to baseline characteristics except FP/SAL treatment status. However, this will be tested by assessing standardised differences for each baseline variable. If substantial differences are noted for important variables, it may be necessary to further adjust the statistical models. This could also include examining the effect of using greedy versus optimum matching approaches in order to obtain the closest propensity score match and/or matching at a ratio other than 1:1.^17^

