**Figure 2 F2:**
[figure not shown]
Flow chart illustrating the planned selection of CPRD participants for objective 1 of the COPD real-world medicines effects study. Note in relation to step 5 (n~18 000) compared with step 1 (n~13 000): approximately 90% of the treated patients will also have been eligible as untreated patients, as they did not receive FP/SAL on their TORCH-eligibility date. This means that they will have at least one period of time during which they are untreated-eligible but then did subsequently go on to receive FP/SAL (meaning they have at least one period of time during which they are treated-eligible). If a person is included as both a treated and untreated participant, they will be contributing different periods of their person-time to each cohort (pre-FP/SAL treatment for the untreated vs post-FP/SAL treatment for treated), and this is handled in the analysis by assigning different index dates. COPD, chronic obstructive pulmonary disease; CPRD, UK Clinical Practice Research Datalink; FP/SAL, fluticasone propionate+salmeterol.

##### Step 1

We will select all patients in the CPRD with COPD who are eligible for HES-linkage and during the period covered by the linkage would have met the following TORCH study inclusion criteria:a diagnosis of COPD;age 40–80 years;smoking history;lung function (forced expiratory volume in 1 s (FEV_1_) <60% predicted, FEV_1_/forced vital capacity (FVC) ratio <70%).

An eligible-for-inclusion date will then be assigned as the date that all of the above inclusion criteria were met for the individual. We will then exclude any individual who has any of the following TORCH study exclusion criteria prior to their eligible-for-inclusion date:a diagnosis of asthma (within the previous 5 years);a diagnosis for any (non-COPD) respiratory disorder;a record of lung surgery;a diagnosis of alpha-1 antitrypsin deficiency;evidence of drug or alcohol abuse;a record of having received long-term oxygen therapy;diagnoses for conditions likely to interfere with the TORCH trial or cause death within 3 years;current use of oral corticosteroid therapy (defined as continuous use for >6 weeks, with courses of oral corticosteroids separated by a period of <7 days considered as continuous use);any exposure to FP/SAL within the previous 4 weeks.

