### Exposures, outcomes and covariates

#### Exposures

For all objectives, exposures will be determined using CPRD prescribing records and code lists for COPD treatments (codelists provided in online supplementary material).

For objective 1, use of FP/SAL (trade name Seretide) is the primary exposure of interest and will be compared with no treatment with FP/SAL. We will limit included patients to those receiving Seretide 500/50, the dose used in TORCH. This information is recorded for all prescriptions of Seretide and this dose is the only currently approved dose for COPD in the UK (although we recognise some prescribing may not follow the licensed indication). If the results for our FP/SAL versus no treatment comparison are not consistent with the TORCH FP/SAL versus placebo results (see the ’Statistical analysis' and ’Validation of results against TORCH' sections for a definition of consistent), we will perform additional analyses where instead of using a no-treatment comparator group, our objective 1 comparator group will be people exposed to SAL, one of the other comparator groups from the TORCH trial.

As a secondary analysis in objective 1, other treatments for COPD will also be compared with no treatment. Selection of unexposed and exposed people for each of these drugs will follow steps 1–6 detailed above in the ’Selection of participants—objective 1' section, although step 3 will be omitted (as these cohorts will not need to be matched to TORCH). The other treatments we plan to include are as follows:LABALAMALABA+LAMA LABA+ICS other than FP/SALLABA+LAMA+ICS.

For objectives 2 and 3, we will again use recorded prescribing information to determine the dose received. We will be reliant mostly on the strength of each individual drug, which is recorded automatically against each product and does not require general practitioners (GPs) to enter these data, ensuring completeness. We will then be able to stratify analyses based on the dose prescribed. Specific exposures for objectives 2 and 3 are as follows (all vs no treatment):FP/SALLABALAMALABA+LAMA LABA+ICS LABA+LAMA+ICS.

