The data analysis for adherence will necessarily be a significant element of the work to be done for this study. However, we have reviewed the records for a random sample of 30 people with COPD starting treatment with FP/SAL to look at adherence patterns over the course of a year. Of the 30 patients, 20 (67%) were still receiving Seretide (FP/SAL) 1 year after starting treatment. Of the 20 who received Seretide for a full year, 15 (75%) received sufficient prescriptions to suggest at least 50% adherence over the year and 8 (40%) had sufficient prescriptions to suggest 80% adherence or higher. As expected, this suggests two things: first, adherence is likely to be poorer in routine clinical care than in the trial population; in TORCH 80% of participants were estimated to have adherence at 80% or higher. Second, there is a wide range of adherence in routine care. This will allow us to estimate both the population-level effects of treatment as actually used in routine care and to estimate the treatment effect in patients with more similar levels of adherence to TORCH participants. While we acknowledge that prescribing can only be a proxy for used medication, we believe it is not an unreasonable assumption that the amount of medication prescribed is correlated with the amount consumed. We plan to assess adherence for the cohort that we select for objective 1 beyond 1 year and report the findings. In the event that objective 1 detects a null or poorer treatment effect than anticipated (rate ratio >0.9), we will conduct a sensitivity analysis restricted to people estimated to be covered by FP/SAL treatment for 80% of their follow-up.

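### The offset in the exacerbation model, log of treated time, is undefined and inconsistent with the intention-to-treat rule in the same paragraph

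*Protocol article*

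**What the plan says.** All of the following is in the protocol article.

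- **Offset.** Methods of analysis specifies a negative binomial model for exacerbations, "with the number of exacerbations as the outcome and the log of treated time as an offset variable". The term treated time is not defined there or elsewhere in the article.
- **Analysis principle.** The same paragraph applies intention-to-treat to all analyses. Once participants enter as exposed or unexposed, "they will remain assigned to that exposure category for the entire duration of their follow-up (irrespective as to whether their true exposure status changes").
- **Window.** Groups are compared by FP/SAL "status for rate of COPD exacerbation, pneumonia and mortality over 3 years".
- **Comparator.** Under Exposures, FP/SAL "is the primary exposure of interest and will be compared with no treatment with FP/SAL".
- **Person-time.** The Figure 2 legend says that a person who appears in both cohorts contributes different time to each: "pre-FP/SAL treatment for the untreated vs post-FP/SAL treatment for treated".
- **Use of the result.** Validation of results against TORCH takes as its reference the "TORCH exacerbations rate ratio for FP/SAL versus placebo (0.75; 95% CI 0.69 to 0.81"). It requires that "the rate ratio for exacerbations in CPRD must be between 0.65 and 0.9", and that the 95% CI exclude 1.
- **Persistence pilot.** Under Handling measurement of adherence to medication: "Of the 30 patients, 20 (67%) were still receiving Seretide (FP/SAL) 1 year after starting treatment".

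**The concern.** A rate model needs the event count and the offset to cover the same period. The intention-to-treat rule puts all exacerbations during follow-up into the count. The offset, as worded, puts only time on treatment into the denominator. The two periods differ whenever a treated participant stops FP/SAL. For an untreated participant who never starts it, there is no denominator at all.

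The exacerbation rate ratio is the only outcome used for the validation decision. A ratio moved by the offset alone could fail the validation rule and set off the contingent analyses: the SAL comparator if the result is inconsistent with TORCH, the analysis restricted to 80% coverage if the ratio exceeds 0.9, and the grace-period analysis if it is below 0.65 or above 0.9. The paragraph covers all objectives, so the same wording carries into objectives 2 and 3.

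**Working it through.** No figure printed in the article depends on the offset, so there is none to reproduce first. The sample sizes of 408 and about 600 per group do not use it.

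**Inputs from the article:** TORCH rate ratio 0.75; validation range 0.65 to 0.9; baseline rate 0.5 per patient per year; about 6000 per group after matching; follow-up up to 3 years. **Assumed:** f, the share of a treated participant's follow-up covered by FP/SAL, shown as a range.

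**Reading A, literal in both groups.** A never-treated participant has treated time 0, and log(0) is undefined. Untreated participants who start FP/SAL later do have some treated time, but one zero is enough to stop the fit. A simulated fit with zero treated time in the untreated group returned no estimates.

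**Reading B, on-drug time for the treated group, follow-up time for the untreated group, all follow-up events counted.** With D events over follow-up T, the treated rate becomes D/(f × T), which is the true rate divided by f. The untreated rate is unchanged. Hence

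estimated ratio = true ratio / f.

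| f (assumed) | True ratio 0.75 becomes |
|---|---|
| 0.95 | 0.75/0.95 = 0.79 |
| 0.90 | 0.75/0.90 = 0.83 |
| 0.833 | 0.75/0.833 = 0.90 |
| 0.80 | 0.75/0.80 = 0.94 |
| 0.70 | 0.75/0.70 = 1.07 |

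The upper limit of 0.9 is crossed at f = 0.75/0.9 = 0.833, and the value 1 at f = 0.75. The article expects a weaker effect in routine care. A true ratio of 0.85 would cross 0.9 at f = 0.85/0.9 = 0.94.

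**Reading C, zero-time untreated records dropped.** Only later FP/SAL starters remain in the untreated group. Their events over all follow-up are divided by a part of it, so the untreated rate is raised and the ratio falls.

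**Reading D, follow-up time in both groups.** Count and offset match, and there is no bias from this source.

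**Simulation check.** 6000 per group, untreated rate 0.5 per year, true ratio 0.75. Assumed: dispersion 1, some loss before 3 years, and coverage varying between people. For reading C, also assumed: about 40% of the untreated start FP/SAL later, with treated time between 5% and 100% of follow-up.

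| Reading | Mean f 0.8 | Mean f 0.6 |
|---|---|---|
| D | 0.746 (95% CI 0.710 to 0.784) | 0.757 (0.720 to 0.795) |
| B | 0.946 (0.900 to 0.995) | 1.305 (1.241 to 1.372) |
| C | 0.398 | 0.516 |

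Reading D recovers 0.75 and meets both validation criteria. Reading B is close to the formula (0.75/0.8 = 0.94; 0.75/0.6 = 1.25). The formula is exact only when f is the same for everyone. Reading C falls below 0.65.

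**The case against.** The strongest reply is that treated time is loose wording for observed person-time in the assigned category. The preceding sentence keeps each participant in that category for all follow-up, and the Figure 2 legend speaks of each cohort contributing its own person-time from its own index date. On that reading the model is sound. This is a fair possibility and nothing in the article excludes it. Nothing confirms it either, and the adherence section plans to estimate the share of time covered by prescribing and to account for it in the analyses. An analyst could therefore build treated time from prescriptions in good faith.

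A second reply is that the literal reading exposes itself, because the software fails. That stands for reading A. It does not help with B or C, which are the repairs an analyst might make after such a failure and which run without warning. Even so, the article describes neither.

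A reader might go further and infer that the pilot puts f at 0.67, so that 0.75 becomes 0.75/0.67 = 1.12. The article does not support this. The 67% is the proportion of 30 people still receiving FP/SAL at one year, not a share of follow-up covered. If the 10 stoppers left evenly over the year and the other 20 were fully covered, first-year coverage would be (20 + 10 × 0.5)/30 = 0.83 and the ratio 0.90. Gaps in prescribing and stopping in years 2 and 3 would lower coverage, and restarts would raise it. The article gives no mean coverage and no pilot data beyond one year.

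A reader might also infer that treated time is zero throughout the untreated group, or that the bias is always upward. The first is untrue of untreated participants who start FP/SAL later. The second is reversed under reading C.

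**Conclusion.** The rule is wrong as written. It names an undefined offset that conflicts with the intention-to-treat principle in the same paragraph, and taken literally it cannot be fitted for untreated participants who never start FP/SAL. This is a stated rule for the validation outcome, not a detail that the article leaves out.

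What follows for the result depends on the reading. Under mixed offsets (B), a true ratio equal to that of TORCH fails the validation range once mean coverage is below about 0.83. This assumes that all follow-up events are counted and that coverage is roughly uniform. If zero-time records are dropped (C), the bias can go downward. If follow-up time was intended (D), only the wording needs correcting. The article does not establish that a biased analysis is planned. It does leave readings that give no fit, a ratio near 0.4 to 0.5, the correct 0.75, or a ratio above 1 from the same true effect.

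**What to change.** In Methods of analysis, replace the log of treated time by the log of follow-up time in both groups. Follow-up time runs from the index date to the earliest of 3 years, death, transfer out or last collection date, and exacerbations are counted over that same interval. Any on-treatment analysis should be specified separately and should count events and time over the same window.

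The cost is one sentence. No extra data are needed and the sample size does not change. If follow-up time was always intended, the change only records that intention.
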